## Abstract

**Background:**

Despite lower mortality rates due to combination antiretroviral therapy, people living with HIV (PLWH) are grappling with increasingly complex health issues, including cognitive impairments in areas such as memory, attention, processing speed, and motor function. Yoga has been shown to be an effective form of exercise and mindfulness-based stress reduction for many clinical populations. However, no randomized trials have evaluated the impact of yoga on cognitive and physical function among PLWH.

**Objective:**

The aim of this pilot randomized trial was to determine the feasibility of a yoga intervention to lay the groundwork for a full-scale, multisite, community-based trial for PLWH. Specific objectives are to (1) assess the feasibility of study protocol and procedures, (2) compare cognition in the yoga group with the usual care control group after 12 weeks of the intervention in PLWH, and (3) compare the effects of the 12-week yoga intervention versus control on balance, walking speed, physical activity, mental health, medication adherence, and quality of life among PLWH.

**Methods:**

We propose a pilot randomized trial with 2 parallel groups (yoga versus control). We will recruit 25 PLWH (>35 years) from community and health organizations in Halifax, Canada. After baseline assessment with blinded assessors, participants will be randomly assigned to the yoga or control group, using a random computer generator. Participants in the yoga group will engage in supervised 60-min group-based yoga sessions 3 times a week for 12 weeks at a yoga studio. Participants in the control group will maintain their current physical activity levels throughout the study.

**Results:**

As per the Consolidated Standards of Reporting Trials extension for pilot studies, means of all outcomes, mean change, and 95% CIs will be calculated for each group separately. Two-tailed independent *t* tests and Fisher exact tests will be used to compare groups at baseline. We will analyze quantitative postintervention questionnaire responses using Chi-square tests, and open-ended responses will be analyzed thematically. Intention-to-treat and per-protocol analyses will be used to analyze secondary variables. Changes in outcome variables will be examined between groups and within groups. Effect sizes will be reported for each outcome. A priori adherence and satisfaction criteria will be met if participants attend >70% of the yoga sessions and if >70% of the participants are satisfied with the intervention as determined by a postparticipation questionnaire. Study enrollment began in January 2018, with results expected for October 2019.

**Conclusions:**

This pilot randomized trial will be the first to investigate the feasibility and effect of a yoga intervention on cognitive and physical outcomes among PLWH. This work will inform the feasibility of further investigations in terms of capacity building, participant recruitment and retention, and assessment and intervention protocols.

**Trial Registration:**

ClinicalTrials.gov NCT03071562; https://clinicaltrials.gov/ct2/show/NCT03071562 (Archived by WebCite at http://www.webcitation.org/785sfhWkw)

**International Registered Report Identifier (IRRID):**

DERR1-10.2196/13818

## Introduction

### Cognitive Impairment in People Living With HIV

Despite lower mortality rates due to combination antiretroviral therapy (cART), people living with HIV (PLWH) are grappling with increasingly complex health issues [1], including cognitive impairments in areas such as memory, attention, processing speed, and motor function [2]. Even with the widespread use of cART, 30% to 60% of PLWH experience cognitive impairment [2,3]. Given that the number of people with HIV-associated cognitive impairment is expected to increase 5- to 10-fold by the year 2030 [4], and the incidence of HIV infection is increasing among older adults [5], this issue has become a public health concern [6]. Aging and HIV appear to have combined deleterious effects on both brain structure and function, and some investigators have hypothesized that these effects could be synergistic [7,8]. As such, the combined effect of age and cognitive impairment in HIV has become a concern over the past decade, especially as PLWH now have a life expectancy that rivals that of their HIV-negative counterparts [9]. Proposed mechanisms for cognitive dysfunction include direct attacks of the virus on brain tissue and indirect processes such as local or systemic inflammation [10]. Glial cells, possible reservoirs for the virus, release proinflammatory cytokines and toxins associated with cognitive disorders and neuron degeneration [11]. Protein gp120 damages neurons by causing calcium overload and reducing brain-derived neurotrophic factor, the central growth factor involved in neurogenesis [12].

HIV-associated cognitive impairment has a profound impact on activities of daily living [13], social function [14], quality of life [15], employment [16], and adherence to pharmacological [17] and nonpharmacological treatment [18]. Despite the fact that ~95% adherence to cART is required for adequate viral suppression, 66% of participants in a HIV clinical trial *simply forgot* to take their medications [19]. Pharmacological adherence is a major priority, given that cART is the mainstay of proper HIV management. A study of 267 adults with HIV revealed that those with cognitive impairment performed worse on functional laboratory measures of shopping, cooking, finances, medication management, and work-related skills than those with normal cognition [20]. Furthermore, the authors discovered that poor executive function, learning, attention, working memory, and verbal abilities strongly predicted functional performance [20]. Authors of another study revealed that symptomatic cognitive impairment was associated with significantly worse scores in 8 domains of the Medical Outcomes Survey for HIV (MOS-HIV) [21]. PLWH with cognitive impairment are less likely to be employed [22], have a difficult time returning to work after disability [23], and have difficulties adapting to the demands of work [20].

### Gait and Balance Impairments Among People Living With HIV

Although the cognitive aspects of HIV-associated neurocognitive disorder such as memory, attention, and processing speed have been studied in great detail, the motor aspects have not received much attention. There is evidence of a shared pathology between cognitive and motor functions; a large study of 1549 PLWH revealed a significant relationship between slowed gait and worsening cognitive function [24]. Balance and gait impairments are common among PLWH [25], and they are associated with frailty, higher rates of falls, and increased mortality [26]. Decreased gait speed is linked to higher fall risk, even in those taking cART with undetectable viral loads [26]. A recent systematic review and meta-analysis of 16 cross-sectional studies and 1 prospective cohort study conducted by Berner and colleagues (2017) evaluated the available literature on gait and balance dysfunction in PLWH [27]; a total of 3 [28-30] of 8 studies [25,26,28-33] that examined gait speed reported slowing of fast gait speeds among PLWH compared with controls.

Balance performance tests also reveal balance impairments among PLWH. Using the Single Leg Stance Time Test, Bauer and colleagues (2011) [25] revealed a significant decrease in nonpreferred single leg stance time among obese PLWH compared with seronegative controls in their sample of 86 seropositive and 121 seronegative individuals. Sullivan and colleagues (2011) [34] had similar findings in their sample of 40 female and male PLWH, but they found no differences between groups in tandem stance time. Using the Single Leg Stance Time Test with eyes closed in their sample of 308 PLWH, Tanon and colleagues (2017) [35] determined that 87% of participants demonstrated balance impairments. Performance on the Heel-To-Toe Walk Test with eyes closed [34], the Limits of Stability Test [25,31], and the 360-Degree-Turn Test (among PLWH with obesity only) [25] may also be impaired. Notably, PLWH appear to perform well on the Berg Balance Scale [26,27,36], which indicates that more challenging dynamic balance assessments are required to identify impairments in this population.

### Exercise and Cognitive Function in People Living With HIV

Quigley and colleagues (2018) recently published a scoping review to map the available evidence regarding physical activity and cognitive outcomes (both objective and self-reported) among PLWH [37]. The scoping review included 16 studies: 5 randomized controlled trials (RCTs) [38-42], 3 pre-post single group observational studies [43-45], and 8 cross-sectional studies [46-53], with a total of 1701 PLWH [37]. The noninterventional research indicated a strong association between physical activity levels and cognitive performance as measured by a cognitive battery in PLWH; all 8 cross-sectional studies demonstrated positive associations [46-53]. However, only 2 of the 8 interventional studies—an RCT [41] of aerobic and resistance exercise and a single cohort study involving Tai Chi [43]—revealed positive outcomes regarding cognition in PLWH. McDermott and colleagues [42] conducted the only RCT to directly examine the effect of exercise on an objective measure of cognition in PLWH. Their 16-week aerobic exercise intervention, 3 times per week at 40% to 75% of heart rate reserve neither had an effect on Montreal Cognitive Assessment scores nor had an effect on Trails A and B scores [42]. However, the sample size comprised 11 participants, and the Montreal Cognitive Assessment may not be sensitive to cognitive impairment in PLWH [54]. Clearly, confirmatory evidence of the effect of exercise on cognition in this population is lacking.

### The Effect of Yoga on Cognitive and Physical Function

Yoga has emerged as an effective form of exercise and mindfulness-based stress reduction across many clinical populations [55]. It is an ancient practice combining postures, mindfulness, spirituality, and breath control to enhance flexibility, strength, and balance, and it is increasingly being recognized as a mainstream intervention to promote a more preventative and holistic health care approach [56,57]. Findings of a meta-analysis of 15 RCTs suggest that yoga interventions lasting 1 to 6 months are associated with enhanced overall cognitive function (Hedges  *g*=0.33), attention and processing speed (Hedges  *g*=0.299), executive function (Hedges  *g*=0.27), and memory (Hedges  *g*=0.18) in people with and without chronic diseases [58]. In fact, it appears that acute bouts of yoga may be superior to aerobic exercise for improving inhibition and working memory, as determined by a repeated-measures study of 30 healthy younger women [59]. There are numerous mechanisms thought to underlie cognitive improvements with yoga interventions. It is possible that yoga may contribute to dominance of the parasympathetic nervous system [60,61] while downregulating the sympathetic nervous system and the hypothalamic-pituitary-adrenal axis [61]. A systematic review of 25 RCTs conducted with healthy and chronic disease populations revealed that those who participated in yoga improved their cortisol levels, heart rate, and blood pressure relative to controls [62]. There is also evidence that yoga and other types of mind-body exercise (including Tai Chi) are associated with improved mood; a meta-analysis of 40 interventional studies revealed that Tai Chi has positive effects on both anxiety and depression [63]. Improvements in the stress response with mind-body exercise may contribute to improved cognitive performance [64]; an RCT of 118 older adults revealed that yoga participants had an attenuated cortisol response and improved executive function relative to the control group following an 8-week yoga intervention [64]. Of note, self-reported mood stress and cortisol levels predicted executive function performance [64]. Other potential mechanisms associated with yoga interventions include the learning of novel tasks, which is associated with changes in brain structure and function [58], sustained attention [65], activation of the default mode network (including learning and consolidation functions) [66], and improved meta-cognition (one’s conscious awareness of his or her cognitive processes), which is closely related to executive function [67].

Yoga is also an effective treatment for impaired balance in people with [68-71] and without physical impairments [72,73] because of its positive effects on strength [74], mobility [69], balance self-efficacy [70,71], and visuospatial memory [75]. A 2016 systematic review and meta-analysis of 6 RCTs confirmed that healthy older adults and individuals with various health conditions, such as stroke, Parkinson’s disease, and knee osteoarthritis, reap yoga-induced benefits to postural stability and mobility [76]. The investigators suggested that health care professionals should recommend yoga to older adults as a safe and effective intervention for balance and mobility limitations [76]. There is considerably less research evaluating the effect of yoga on balance, quality of life, and depression in PLWH. In their case-series study of 3 PLWH, Kietrys and colleagues (2018) observed improvements in several gait parameters (including double-limb support time, step length, stride length, stride velocity, and walking velocity) and balance (as measured by the Multidirectional Reach Test) in 2 of the 3 participants following a 4-week yoga intervention [77]. There is some RCT evidence for the benefits of yoga on quality of life [78] and depression [79] in PLWH; however, the former study did not involve yoga postures, and the latter intervention was only a month in total duration. To date, no RCTs have evaluated the impact of yoga on cognitive and physical performance among PLWH.

### Purpose and Objectives

The purpose of this pilot RCT is to determine the feasibility of a yoga intervention to lay the groundwork for a full-scale, multisite, and community-based trial with PLWH. Specific objectives are to (1) assess the feasibility of the study protocol and procedures, (2) compare cognitive function in PLWH in a yoga intervention group with a usual care control group among PLWH after 12 weeks of the intervention, and (3) compare the effects of the 12-week yoga intervention versus control on balance, walking speed, physical activity, mental health, medication adherence, and quality of life in PLWH.

## Methods

### Design

We propose a pilot randomized trial with 2 parallel groups, comparing the yoga group with a usual care control group using quantitative methods of data collection. Figure 1 outlines the sequencing of the study protocol. The conceptual framework for pilot and feasibility studies created by Eldridge and colleagues [80] and the Consolidated Standards of Reporting Trials (CONSORT) 26-item checklist for randomized pilot and feasibility studies will be employed to ensure methods are properly defined and reported [81]. The study is guided by a community advisory committee comprising 7 members of the HIV community and 3 representatives from local HIV organizations. Our research team held consultations with the community advisory committee to assist with study design and recruitment strategy.

**Figure 1 figure1:**
[figure not shown]
Consolidated Standards of Reporting Trials flow diagram.

### Participants

We will identify cognitive concerns on the Communicating Cognitive Concerns Questionnaire (C3Q) with a cut-off of 35 points or less [82]; in addition, we will include a maximum total of 25 PLWH who are aged 35 years or older of any gender, are English speaking, live within 50 km of the study site, are able to provide informed consent, and are deemed medically stable as assessed by the Physical Activity Readiness Questionnaire Plus [83]. Study exclusion will include regular participation in a yoga program during the 6 months before study commencement.

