#### Assessment Protocol

As per the CONSORT extension for pilot RCTs, the number of participants screened for eligibility, randomly assigned, received intended treatment, and assessed for each objective will be recorded [81]. Study data will be collected in the Physiotherapy department at Dalhousie University and managed using Research Electronic Data Capture (REDCap) software (REDCap Inc) [87]. The authors will provide access to the study’s REDCap (REDCap Inc) data upon request. Table 2 outlines the outcome variables and measurement tools.

**Table 2 table2:** Outcomes and measurement tools.

Outcome	Measurement tool	Objective measure or self-report
Yoga readiness (previous experience with yoga, injuries and ability level)	Yoga readiness questionnaire (yoga group only)	Self-report
Cognitive performance	Communicating Cognitive Concerns questionnaire; Brief Cognitive Ability Measure	Self-report; objective
Motor function (balance, walking speed)	Community Mobility and Balance Scale; 10-meter walk test	Objective; objective
Mental health	Hospital Anxiety and Depression Scale	Self-report
Quality of life	Medical Outcomes Survey	Self-report
Medication adherence	Simplified Medication Adherence Questionnaire	Self-report
Physical activity	Rapid Assessment of Physical Activity; Fitbit Flex 2—total distance walked (km) and steps taken per day	Self-report; objective
Participant satisfaction, safety, comfort, fatigue, and benefits	Postparticipation survey (yoga group only)	Self-report

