##### Secondary and Tertiary Measures

Cognition, physical performance (balance, walking speed), physical activity, and affective (mental health, quality of life, and medication adherence) evaluations will be administered at baseline and postintervention (12 weeks) by a trained assessor, blinded to the group assignment. The rationale for blinding the assessor is to reduce bias in scoring during the assessment sessions. The estimated length of time for the assessment sessions is 2 hours per participant. We will measure *cognitive function* using the Brief Cognitive Ability Measure (B-CAM), a computerized cognitive test developed for PLWH, using Rasch measurement theory and analysis that takes 30 min to administer [88,89]. The B-CAM provides a measure of global cognition that is calibrated—the intervals between logits are equal, meaning the data are continuous [88,90].

Cognitive domains tested with the B-CAM include visual detection (reaction time), Flanker task (response inhibition) [91], memory (learning and recall of 8 words), Shape 2-back (working memory) [92], Corsi block-tapping forward and back tests (visuospatial memory) [93], verbal fluency (letters F-A-S in English) mini Trail Making Test B (executive function) [94], and the Tower of London test (planning) [95]. The scoring of the B-CAM ranges from 0 to 24, with higher values indicating better global cognition [90]. To reduce the likelihood of practice effects, different versions of the B-CAM are performed at baseline and final assessments [90]. Group-based trajectory analysis has revealed that no practice effects were found at the item level [90].

Self-reported cognition will also be assessed using the C3Q, an 18-item paper-based questionnaire that was developed to estimate the presence and frequency of memory, attention, executive function, visuospatial, speech and language, behavior and emotion, and cognitive challenges among PLWH [82]. The frequency of such challenges are recorded by the participant on a 3-point scale: frequently (almost every day), sometimes (once a week), or rarely (once a month) [82].

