## Results

### Data Analysis

All questionnaires and measures will be assessed for missing data. The data will be analyzed to determine if the assumptions for parametric tests are met. Descriptive statistics will be used to characterize the participants. As per the CONSORT extension for pilot studies, means of all outcomes, mean change, and 95% CIs will be calculated for each group separately. We will also follow the Sex and Gender Equity in Research guidelines [108] by disaggregating data by sex and gender. Participant dropouts will also be reported disaggregated by sex.

Independent *t* tests and Fisher exact tests will be used to compare the 2 groups at baseline. If the 2 groups differ at baseline, that variable will be included in the analysis as a covariate. We will analyze quantitative postintervention questionnaire responses using Chi-square tests, and open-ended responses will be analyzed thematically. Intention-to-treat and per-protocol analyses will be used in the analysis of the secondary variables. Changes in outcome variables will be examined between groups and within groups. Floor and ceiling effects will be calculated for the CB&M test. Effect sizes will be reported for each outcome. Alpha level will be set at .05, using 2-tailed for all inferences, and data will be analyzed with SPSS Version 25 (SPSS Inc). As this is a pilot study, sample size calculations are not recommended [81]. This pilot study will not be adequately powered to conclusively state the influence of the intervention on study outcomes, but if trends are promising, a future, more adequately powered trial will be planned. This pilot study will provide preliminary data for future sample size calculations.

Study enrollment began in January 2018, with results expected in October 2019.

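### The C3Q is both the entry screen and an outcome, so within-group C3Q change is open to regression to the mean; the randomised comparison is not

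*Protocol article*

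**What the plan says.** The Participants section opens with the screen: "We will identify cognitive concerns on the Communicating Cognitive Concerns Questionnaire (C3Q) with a cut-off of 35 points or less". The other criteria follow after a semicolon: "in addition, we will include a maximum total of 25 PLWH who are aged 35 years or older of any gender". The linkage suggests that the cut-off is an inclusion criterion, though the wording is loose.

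The C3Q returns as an outcome. Table 2 lists under cognitive performance "Communicating Cognitive Concerns questionnaire; Brief Cognitive Ability Measure", the first labelled self-report and the second objective. The Secondary and Tertiary Measures section says "Self-reported cognition will also be assessed using the C3Q, an 18-item paper-based questionnaire", answered on a "3-point scale: frequently (almost every day), sometimes (once a week), or rarely (once a month"). It gives no item codes, total range or direction for the C3Q, although it gives range and direction for the B-CAM. On timing, the evaluations "will be administered at baseline and postintervention (12 weeks) by a trained assessor, blinded to the group assignment". No separate screening administration of the C3Q is described.

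The Data Analysis section then says: "Changes in outcome variables will be examined between groups and within groups". It promises an effect size for every outcome and sets a two-tailed alpha of .05 for all inferences. It also says that a larger trial will be planned if the trends look promising.

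**The concern.** People chosen because they scored poorly on a scale tend to score better the next time, simply because part of the poor score was chance. When the scale that decides entry is also the scale on which change is measured, and the entry score doubles as the baseline, this regression to the mean appears as improvement in every arm, treated or not.

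The plan treats within-group and between-group change alike, under the same alpha. A within-arm C3Q gain in the yoga group could therefore be read as an effect of yoga, and could count as a promising trend when the larger trial is considered. A comparison of within-arm results, with improvement declared in one arm and not the other, would not repair this, because it is not a test of the difference between arms.

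**Working it through.** **Inputs from the article.** Cut-off 35 or less (Participants); 18 items, three response categories, assessment at baseline and 12 weeks (Secondary and Tertiary Measures); between- and within-group change, alpha .05 two-tailed (Data Analysis); 1:1 randomisation after the baseline assessment (Randomization).

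**Inputs not given, so assumed.** The share p of screened people who qualify; the test-retest correlation r; the item coding; a roughly normal score with the same mean and variance on both occasions when there is no effect; the screening score reused as baseline. The plan derives no figure on this point, so there is none to reproduce.

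**Step 1: what the cut-off admits.** Two natural codings make a low score mean more concerns.
- Items coded 0-2: the range is 0 to 18 × 2 = 36. A score of 35 or less covers 36 of the 37 possible totals and excludes only a person who answers rarely to all 18 items. With independent items and assumed probabilities for frequently/sometimes/rarely, 98% are admitted at .05/.15/.80 and 60% at .01/.04/.95.
- Items coded 1-3: the range is 18 × 1 = 18 to 18 × 3 = 54, with midpoint 36. A score of 35 or less covers 18 of 37 totals. About 0% are admitted at .05/.15/.80, 4% at .2/.3/.5, 44% at one third each and 93% at .5/.3/.2.

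The admitted share could therefore be almost anything, so the next step uses a range.

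**Step 2: expected shift in each arm.** When people enter with a score below a cut at standard normal point z, where p = Φ(z), the mean baseline score lies φ(z)/p below the population mean. On retest a fraction 1 − r of that gap closes by itself:

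shift in SD units = (1 − r) × φ(z)/p

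For p = 0.5, φ(0)/0.5 = 0.399/0.5 = 0.80. The shift is 0.1 × 0.80 = 0.08 at r = 0.9 and 0.3 × 0.80 = 0.24 at r = 0.7.

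| Share admitted | z | r = 0.9 | r = 0.8 | r = 0.7 |
|---|---|---|---|---|
| 31% | −0.5 | 0.11 | 0.23 | 0.34 |
| 50% | 0 | 0.08 | 0.16 | 0.24 |
| 69% | 0.5 | 0.05 | 0.10 | 0.15 |
| 84% | 1 | 0.03 | 0.06 | 0.09 |

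These are SDs of the unselected population. Selection also narrows the baseline spread: at p = 0.5 the SD of those admitted is about 0.60 of the original. If a within-arm effect size were divided by that narrower SD, the same shift would read as 0.08/0.60 = 0.13 to 0.24/0.60 = 0.40.

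**Step 3: the randomised contrast.** Both arms are drawn from the same selected group and are allocated after baseline, so each carries the same expected shift. In the difference between arms the expected contribution is shift − shift = 0.

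**The case against.** The case on the other side is substantial. The trial is a pilot whose primary measures are feasibility. The C3Q is one of two cognition measures, and the objective on cognition is a comparison of yoga with control, which randomisation protects. The article disclaims power for conclusions about effect. Nowhere does it say that the screening score is reused as baseline, and both r and the admitted share above are assumptions. A condensed article may leave scoring to the cited source. Nor should the shifts be set against the pooled effect of 0.33 for overall cognition in the Introduction: that figure comes from randomised trials, not from within-arm change on a self-report scale. All of this stands and limits the point to within-arm C3Q change. It does not remove it, because within-group change is planned without any distinction in the inference drawn from it.

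Two stronger readings are tempting. The first is that 35 cannot work as a cut-off on this scale, either because it admits nearly everyone or because it selects in reverse. The article does not support this. With 1-3 coding and higher meaning fewer concerns, the cut-off separates many from few concerns; with 0-2 coding in that direction it is lenient but points the right way. Counting 36 of 37 totals counts scores, not people. Reverse selection would require the cited cut-off to have been applied backwards, and nothing in the text says so. The second is that the yoga-control comparison of cognition is biased; step 3 shows that it is not.

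**Conclusion.** The concern holds for within-group C3Q change only. If the cut-off is applied at entry, a low score means more concerns and the screening score serves as baseline, each arm's expected C3Q change contains an artefactual improvement. It is about 0.08 to 0.24 SD if half are admitted and r is 0.9 to 0.7, and about 0.03 to 0.34 SD over admitted shares of 84% to 31%. It is smaller still if the cut-off excludes almost nobody, and absent if the cut-off is not used to select. The between-group contrast is unbiased in every case. The size rests on assumptions that the article does not let a reader check. The remedy does not depend on that size.

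**What to change.** In Data Analysis, state that any inference on the C3Q rests on the between-arm comparison. Report within-arm C3Q change descriptively, and do not treat it as an effect of yoga or as a trend that supports a larger trial. Where possible, use a C3Q score taken at the baseline visit and separate from the screening score, so that most of the regression occurs before the baseline is measured.

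As a clarification only, give the C3Q range and direction beside the cut-off in Participants, as is already done for the B-CAM, and say whether meeting it is required for entry.

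The cost is small: within-arm C3Q tests are given up, the 18-item paper questionnaire may have to be repeated once at baseline, and a few sentences change. For participants already enrolled without a separate baseline score, the change in inference alone is enough.
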